**Figure 5 F5:**
[figure not shown]
Flow diagram for participants' enrollment, randomisation, allocation, and follow-up (CONSORT, 2010).

### Criteria for Discontinuing or Modifying Allocated Interventions

The study intervention will be discontinued by trial investigators if any participants have deteriorated health status, exhibited any unexpected adverse effects towards the TPS intervention, or withdrawal of participant consent. The trial investigators will either modify or discontinue the intervention. Nonetheless, study participants will be retained in the trial to enable follow-up data collection and prevent missing data.

### Strategies to Improve Adherence to Interventions

**Fidelity of the intervention:** To ensure the fidelity of the intervention, the project team will ascertain whether the interventions are delivered as designed. A WhatsApp message reminder (e.g., TPS intervention schedule, fMRI scan appointments, and f/u appointments) will be delivered to participants to monitor their progress and adherence throughout the TPS study.

### Interventions—Concomitant Care

Participants will be instructed continue to take their prescribed medications for other conditions as normal. Self-prescription of any psychotropic medications to mitigate depressive symptoms is strongly discouraged to avoid contamination of data. Throughout the intervention period, participants will be advised to avoid strenuous exercise and adhere to healthy lifestyles and regular resting periods.

### Provisions for Post-trial Care

Participants who are finished receiving the TPS treatment will have a follow-up assessment at a 3-month period. They could contact the PI during the post-trial for any potential physical or mental health issues related to the TPS treatment.

## Outcomes

### Outcome Measures (Primary and Secondary Outcomes)

#### Baseline Assessments

##### Diagnostic Interview

The diagnosis of MDD will be confirmed using the Structured Clinical Interview for Diagnostic and Statistical Manual of Mental Disorders (SCID-5).

##### Demographic Data

We will solicit the demographic data of the patients, including age, gender, educational attainment, place of birth, marital status, number of children, financial condition, family history of depression/mood disorders, and family household income. Medical comorbidities will be assessed with the Cumulative Illness Rating Scale (CIRS). The handedness of the participants will be evaluated using the Edinburgh Handedness Inventory—Short Form. Participants' medical and psychiatric history, including the age of onset of major physical illnesses, depressive symptoms (with or without current medication), and treatment /drug dosage, will also be recorded at baseline.

#### Primary Outcomes

##### Depression

Hamilton Depression Rating Scale-17 (65) will be used to measure symptoms of depression and participants' mood and depression severity. HAM-D-17 is a widely used reliable measurement of depressive and mood symptoms. Scores will range from 0 to 52, with higher scores indicating more severe depression. Clinical response will be defined as a reduction of 50% or more in the HAM-D-17 score. A HAM-D-17 score of 7 or less will be used as an indicator of remission.

#### Secondary Outcomes

##### Anhedonia

The core symptom of depression will be assessed by the Chinese version of the Snaith-Hamilton Pleasure Scale (SHAPS; clinical utility of the SHAPS in Chinese settings). SHAPS is a 14-item scale assessing participants' hedonic experience in the last few days. SHAPS includes four domains (interest/pastimes, social interaction, sensory experience, and food/drink), rated on a 4-point Likert-type scale (1, Definitely Agree; 2, Agree; 3, Disagree; 4, Definitely Disagree). Total score will range from 14 to 56, with higher scores representing more pronounced anhedonia. It is one of the most widely used self-report questionnaires in clinical research for evaluating anhedonia with good psychometric properties (66).

#### Instrumental Activities of Daily Living (IADL)

Instrumental activities of daily living will be assessed by the Hong Kong Chinese version of the Lawton Instrumental Activities of Daily Living Scale. This IADL is a valid and reliable tool to assess the daily functioning of Hong Kong adults (67). The scale encompasses nine activities which include the ability to use the telephone, shopping, food preparation, housekeeping, laundry, home maintenance, transport, ability to handle finances, and responsibility for own medication. Participants will be instructed to indicate their ability on a 4-point Likert scale (0, Definitely not; 1, Need some help; 2, Can do it by myself but with some difficulty; 3, Do not need any help). The total score of the IADL will range from 0 to 27, with higher scores indicating more independence in activities of daily living.

#### Cognition

Global cognition will be measured using the Hong Kong Chinese version of the Montreal Cognitive Assessment (MoCA) (68). The MoCA is a one-page test with a maximum score of 30. One point is added if the person has 12 years of education or less. A score of 23–26 represents mild cognitive impairment, 17–22 represents moderate impairment, and 16 or below suggests severe impairment and dementia. Working memory, executive function, and attention will be measured by forward and backward digit span, the category verbal fluency test, and the Trail Making Test (TMT) Parts A and B.

#### Neuroimaging

Participants will receive pre- and post-treatment MRI scans to measure any changes in structural and functional connectivity changes in the brain. Structural MRI, diffusion tensor imaging (DTI), and resting state-fMRI (rs-fMRI) will be performed using a 3T scanner at the University Research Facility in Behavioural and Systems Neuroscience, The Hong Kong Polytechnic University. The subjects will be closely monitored by the research assistant and the radiographer during scanning. The whole scan will last around 45 min including preparation. Structural MRI scans, including T1- and T2-weighted fluid attenuation inversion recovery (T2-FLAIR) sequences, will be used for assessing regional volume differences across the whole brain. High resolution sagittal 3D T1-weighted [spoiled gradient recalled echo (SPGR)/magnetisation-prepared rapid gradient echo (MPRAGE)] images of 1 mm x 1 mm x 1 mm were acquired with repetition time (TR) = 1,820 ms, echo time (TE) = 3.75 ms, inversion time (TI) = 1,100 ms, and flip angle = 70°. This will be followed with axial 2D-T2-weighted FLAIR images of 0.9 × 0.9 × 3 mm, which will be acquired with TR = 9,160 ms, TE = 90 ms, TI = 2,500 ms, and flip angle = 150°, for the quantification of white matter hyperintensities (WMH). DTI sequence will be conducted using a single-shot spin-echo echo-planar imaging, with diffusion-sensitising gradients applied along 16 non-collinear directions with diffusion weighting factor b = 1,000 s/mm^2^ and two b = 0 images. The imaging parameters were the following: TR/TE = 1,200/82 ms, matrix size = 128 × 128, field of view (FOV) = 240 mm, slice thickness = 3 mm with no intersection gap, number of excitations = 2, and number of slices = 67. Finally, resting-state fMRI of 150 T2-weighted gradient echo-planar imaging (EPI) will be acquired with TR = 2 s and TE = 32 ms, with 32 slices, and a resolution of 3 × 3 × 4 mm, during which subjects will view a fixation cross (“+”) passively at the centre of the screen. Images processing and analysis will be performed using software packages including FSL (http://fsl.fmrib.ox.ac.uk/fsl/fslwiki/), Freesurfer, and SPM8 (Oxford, UK). Total brain and its total grey and white matter volumes will be extracted from the T1 structural scan. Grey matter and white matter tissue maps will be segmented and compared for regional tissue density differences using voxel-based morphometry (VBM) (69). Structural connectivity will be assessed by fractional anisotropy (FA) maps extracted from DTI imaging.

For functional connectivity, all resting state-fMRI (rs-fMRI) volumes will be pre-processed, with motion correction and slice timing correction, and then linearly registered to the Montreal Neurological Institute (MNI) standard space. A data-driven approach will be used for the analysis of rs-fMRI data. Independent component analysis will be done with Multivariate Exploratory Linear Decomposition in FSL. A set of independent components will be identified as the common resting-state functional networks. The global and local efficiency, modularity, and hubs will be computed using the Brain Connectivity Toolbox (https://sites.google.com/site/bctnet/). A dual regression approach will be used to investigate between-group differences in the individual functional networks. The significance threshold of the voxel-wise differences will be set at *p* < 0.05 (family-wise error corrected).

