## Methods: Participants, Interventions, and Outcomes

### Study Setting

#### TPS Treatment Setting and Treatment Procedures

The TPS intervention will be performed at the Integrative Health Clinic, The Hong Kong Polytechnic University. The principal investigator (PI)-licenced medical staff/other trained medical professionals will deliver the intervention. The TPS system consists of a mobile single transducer and an infrared camera system for MR-based neuro-navigation (NEUROLITH, Storz Medical AG, Tägerwilen, Switzerland). TPS generated single ultrashort (3 μs) ultrasound pulses with typical energy levels of 0.2–0.25 mJ/mm^2^ and pulse frequencies of 4–5 Hz (pulses per second). During the TPS session, participants will sit in a comfortable chair in the treatment venue. Participants will wear a BodyTrack system consisting of a 3D camera, tracking glasses with markers, and a TPS handpiece with markers (Figure 1). This BodyTrack system (STORZ MEDICAL AG) will ensure that the participants' heads match with their MRI data so that each applied pulse can be visualised and documented in real-time. Real-time tracking of the handpiece position enabled automatic visualisation of the treated brain region. The energy applied will be highlighted in green colour as shown in Figure 2.

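### The resting-state fMRI plan commits to linear registration and names no motion clean-up beyond realignment, which costs sensitivity and leaves a pre/post connectivity change open to motion confounding

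*Protocol article*

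**What the plan says.** The Neuroimaging section of the protocol article sets out the functional connectivity analysis as a chain of steps. The volumes "will be pre-processed, with motion correction and slice timing correction, and then linearly registered to the Montreal Neurological Institute (MNI) standard space". Then "Independent component analysis will be done with Multivariate Exploratory Linear Decomposition in FSL", and "A set of independent components will be identified as the common resting-state functional networks". For graph measures, "The global and local efficiency, modularity, and hubs will be computed using the Brain Connectivity Toolbox". The group test follows: "A dual regression approach will be used to investigate between-group differences in the individual functional networks", with the voxel-wise threshold at p < 0.05, family-wise error corrected.

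The same section provides for "High resolution sagittal 3D T1-weighted" images at 1 mm in each direction, and names FSL, Freesurfer and SPM8 among the software. The resting-state run is 150 volumes at a repetition time of 2 s.

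Three other places matter:
- Objectives words the imaging aim as the post-treatment scan compared with the pre-treatment scan.
- Trial Design has all subjects in each group scanned before and after the TPS sessions. Intervention Description and Limitations of This Study give the waitlist group the same TPS at a different time.
- Data Analysis Plan describes within-group and between-group comparison of pre and post scans for voxel-based morphometry. It names no motion variable for any imaging comparison.

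**The concern.** There are two separate weaknesses, with different consequences.

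The first is a stated choice. A linear transform corrects position, scale and shear but cannot bring local anatomy into line across people. Residual misalignment blurs a real effect in the group map, so with about 15 per arm the plan is more likely to miss a true change.

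The second is a gap in the chain of named steps. Realignment puts volumes back in position but leaves motion-related signal in the time series, and that signal can shift network maps and graph measures. The independent component analysis is described as a way to find networks, not to remove noise components. If motion differs between the first and second scan, a pre/post difference in connectivity can appear without any neural effect of TPS. A reader of Objective 5 would then have no means of telling the two apart.

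**Working it through.** **No figure to reproduce.** Sample Size gives 30 participants without an effect size, standard deviation or power. No motion or registration-error figure appears anywhere. The passages therefore carry the argument, and the arithmetic is illustration under assumed inputs.

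**Registration.** The stated step is linear. The T1 needed for a nonlinear step is acquired for every participant, and the named software supports that step. The direction of the cost is clear: less sensitivity. Nothing in it favours one arm or one scan, so it does not by itself generate a false difference.

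**Motion, by contrast tested.**
- Pre/post change (as in Objectives): a motion shift between scans is fully mixed with any TPS effect.
- Between arms (the only resting-state test stated in Neuroimaging), both arms scanned over the same interval: a shift common to both arms cancels in expectation. Bias needs motion to differ by arm.
- Whether the waitlist group has a scan pair over an untreated interval is unclear. Trial Design can be read as placing each participant's two scans around that participant's own TPS course.

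**Illustrative error rates.** Assumed: correlation of motion with the connectivity metric 0.3 to 0.5; motion 0.5 SD lower at the second scan, or in one arm; pre/post correlation 0.5.
- Metric shift m = 0.3 × 0.5 = 0.15 SD, to 0.5 × 0.5 = 0.25 SD.
- SD of change = √(2 × (1 − 0.5)) = 1, so m is also in change-score SDs.
- Noncentrality is m√n for a paired test and m√(15/2) for 15 versus 15. Rejection rates are from the noncentral t, single test, two-sided 0.05, with no TPS effect.

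| Contrast | m = 0.15 | m = 0.25 |
|---|---|---|
| Pre/post, n = 30 | 12.5% | 26.3% |
| Pre/post, n = 15 | 8.4% | 14.7% |
| 15 v 15, shift in one arm only | 6.8% | 10.1% |
| 15 v 15, same shift in both arms | 5% | 5% |

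**Illustrative dilution.** For an assumed true d = 1.0 at 15 per arm, with the effect multiplied by a, noncentrality is a√7.5. Power is 0.753 at a = 1, 0.663 at 0.9, 0.562 at 0.8 and 0.457 at 0.7.

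For a single Gaussian focus, peak retention is (s²/(s² + d²))^1.5 with s = FWHM/2.355, where d is here the residual misalignment SD per axis. With assumed FWHM of 8 to 12 mm and misalignment SD of 2 to 3 mm:
- FWHM 8 mm: s² = 11.54, giving 0.64 (2 mm) and 0.42 (3 mm).
- FWHM 12 mm: s² = 25.97, giving 0.81 (2 mm) and 0.64 (3 mm).

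None of these inputs comes from the documents. The table does not give the error rate of the family-wise-corrected voxel-wise test, and the height of a small focus is not the relevant quantity for whole-brain efficiency or modularity.

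**The case against.** **The article does not say that its list of steps is complete.** Denoising, displacement limits and motion covariates are details that an article commonly leaves to a fuller document. This stands: a reader might infer that the pipeline uses only three pre-processing steps, and the text does not support the word only. What can be said is that the steps named include no such clean-up. The linear registration is different, because it is stated rather than left out.

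**The stated test is between groups.** Familiarity with the scanner cancels if both arms are scanned concurrently. This also stands, and the last row of the table shows it. It does not protect the pre/post comparison in the objective, and the untreated scan pair is not guaranteed by the text. That is a question of control timing, which denoising cannot settle.

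**Arm-specific motion is conjecture.** A reader might infer that treated participants learn to lie still over six sessions, since "Participants will wear a BodyTrack system consisting of a 3D camera, tracking glasses with markers, and a TPS handpiece with markers", or that better mood makes them less restless. The documents support neither. They describe sitting in a comfortable chair while a camera matches the head to the MRI data, and they report no motion data.

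**Anatomical spread may be modest.** The inclusion criteria set no upper age, but the objectives concern young adults and recruitment runs through two universities. This limits what registration can be costing, though it does not make the linear step the better choice.

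**Motion adjustment has its own cost.** Motion is measured after randomisation. If treatment affects it, excluding scans by motion or adjusting for it can bias the randomised comparison or remove part of a real effect. This stands and shapes the fix.

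**Conclusion.** The point holds in two limited parts. First, the plan commits to linear registration when its own data and software allow better. This loses sensitivity by an amount that the documents do not allow to be quantified, and it does not by itself create a false TPS effect. Second, the named steps contain nothing beyond realignment to remove motion-related signal before the component analysis, dual regression and graph measures. A pre/post connectivity change under Objective 5 is therefore open to motion confounding. A between-arm comparison of concurrently scanned arms is affected only if motion differs by arm.

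A reader might infer from the illustrative figures that false-positive rates of up to 26% are to be expected. The documents do not support that: the figure needs an uncontrolled pre/post test in all 30 participants and motion inputs that are wholly assumed. Importance is minor. This is one modality of a secondary objective in a self-described pilot, and the HAM-D-17 primary outcome is untouched.

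**What to change.** In the Neuroimaging section:

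1. Replace the linear step with boundary-based registration of each functional scan to the participant's own T1, followed by nonlinear T1-to-MNI registration.
2. Add motion denoising within each scan before dual regression and graph analysis: either ICA-based removal of noise components, or regression on motion parameters with white-matter and CSF signals.
3. Report mean framewise displacement by arm and by scan. Use displacement adjustment or exclusion only as a pre-specified sensitivity analysis, because motion is a post-randomisation variable that treatment may affect.
4. Rest any claim of a TPS effect on connectivity on the between-arm comparison, not on the uncontrolled pre/post change. State whether the waitlist group has a scan pair over the same untreated interval, since that comparison depends on it.

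Trial Status reports recruitment complete, so the analysis is the part still open to change. No new scans are needed for steps 1 to 3. The cost is more analysis time and some loss of temporal degrees of freedom, which matters somewhat in a run of 150 × 2 s = 300 s, or 5 minutes.

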**Secondary objectives**:

To improve young adults' anhedonia symptoms after the 2-week TPS intervention and will be maintained at 3-month post-intervention follow-upTo improve young adults' instrumental activities of daily living (IADL) after the 2-week TPS intervention and will be maintained at 3-month post-intervention follow-up.To improve young adults' cognition after the 2-week TPS intervention and will be maintained at 3-month post-intervention follow-up.Post-MRI scan will show a remarkable structural and functional connectivity in participants' brains after the 2-week TPS intervention compared to pre-MRI scan.

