### Statistical Methods

#### Statistical Methods for Primary and Secondary Outcomes

##### Data Analysis Plan

Data will be analysed by the SPSS for Windows, version 27. The normality of the primary outcome (depression) scores will be tested by the Kolmogorov-Smirnov test. If significant differences between sociodemographic variables are found, covariates will be used as a control or confounding variables in the main analysis. For Objective 1, multilevel modelling analysis will be used to investigate changes in the outcome measures (depression) at each time interval (2 weeks and 3 months) with respect to their baseline measurements to examine the effects of TPS. A two-level model will be built, with repeated time points at level 1 and respondents at level 2. The baseline difference between groups will be tested using the Wald test based on the regression coefficient estimates of the indicator. The changes in the outcome measures over time will be included in the fixed part of the model to estimate change from baseline to 2 weeks and from baseline to 3 months. To assess the effects of TPS over time, interaction terms will be included in the fixed part of the model. The significantly different demographics between groups identified in step one of the analysis and other possible confounders will be adjusted by including them in the main-effect model. The within-respondent random effects of the outcome measurements will be taken into account by the level-2 variance in the model. For Objectives 2, 3, and 4, pairwise comparison and other hypotheses on the intervention effects will be tested using a generalised Wald test with an adequate degree of freedom from the modelling analysis (70). The same model, which will be conducted separately for each outcome, will be used to investigate the effect of interventions on secondary outcome measures. To assess the effects of TPS, an intention-to-treat (ITT) analysis will be performed on all participants who undergo random allocation. A multiple imputation method will be used to handle missing data. The pooled results of the multilevel analyses with five multiple imputations will be presented. A sensitivity analysis will be performed by comparing results from analysis datasets with and without missing data imputation. In all tests, significant differences between groups will be detected with a 95% CI, and *p*-values of < 0.05 (two-tailed) will be considered significant. For Objective 5, the neurological rs-fMRI data, longitudinal VBM will be used to examine whether TPS produces local changes in grey matter. Specifically, relative local increases and decreases between pre- and post-intervention scans will be compared within and between study groups. The diffusion MR data will be analysed using the diffusion tensor model. After a mathematical diagonalization process, the eigenvectors and eigenvalues describing the tensor ellipsoid will be determined. Then, two standard diffusion indices will be obtained which are the following: (1) the apparent diffusion coefficient and (2) the fractional anisotropy. DTI scans pre- and post-treatment will permit the assessment of changes in axial diffusivity, with lower values being interpreted as the structural enhancement of white matter. For the cognitive data analysis, general linear modelling (GLM) will be used to compare the difference in performance in the forward and backward digit span, the Stroop test, the category verbal fluency test, and the TMT Parts A and B between the TPS group and the waitlist control group. Performance on the TMT between the TPS group and the waitlist control group will be analysed by one-way repeated-measures ANOVA. Participants' narrative feedback on TPS will be analysed with descriptive content analysis.

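### The imaging family-wise correction is stated for voxels but not across networks, so its 5% error rate does not hold for Objective 5

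*Protocol article*

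**What the plan says.** The Neuroimaging section describes a data-driven analysis by independent component analysis: "A set of independent components will be identified as the common resting-state functional networks". The number of networks is not given. The group test follows: "A dual regression approach will be used to investigate between-group differences in the individual functional networks". The next sentence sets the error rate: "The significance threshold of the voxel-wise differences will be set at *p* < 0.05 (family-wise error corrected". The same section adds graph measures: "The global and local efficiency, modularity, and hubs will be computed using the Brain Connectivity Toolbox".

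The Data Analysis Plan gives a general rule that p-"values of < 0.05 (two-tailed) will be considered significant". For Objective 5 it then lists longitudinal voxel-based morphometry (VBM), apparent diffusion coefficient (ADC), fractional anisotropy (FA) and axial diffusivity. For the VBM changes it says that "relative local increases and decreases between pre- and post-intervention scans will be compared within and between study groups".

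Under Secondary objectives, the expectation is worded as a pre-to-post result: "Post-MRI scan will show a remarkable structural and functional connectivity". No network, modality or measure is singled out as the one that decides the objective.

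**The concern.** A family-wise rate of 5% means something only for a defined family of tests. Here the correction is attached to voxels, while the group test is repeated in each network. Read as written, each network carries its own 5% chance of a false positive, and the objective is judged over all of them.

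Within-group comparisons raise a separate problem. A pre-to-post change in the TPS arm alone cannot be separated from natural course, regression to the mean or scan-to-scan drift. The waitlist arm exists to remove these. If such a change can count towards Objective 5, the randomised comparison is bypassed.

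At stake is a secondary objective in a 30-person trial. A chance finding in one network, or an uncontrolled within-group change, could be presented as mechanistic support for TPS.

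**Working it through.** **Inputs.** The voxel-wise threshold is 0.05, family-wise corrected (Neuroimaging). The general threshold is 0.05, two-tailed (Data Analysis Plan). There are four graph measures: global efficiency, local efficiency, modularity and hubs (Neuroimaging). There are three diffusion measures: FA, ADC and axial diffusivity (Data Analysis Plan). The number of networks, K, is not stated; 5 to 20 is my assumption.

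**Step 1, the plan's own figure.** The 0.05 is a chosen setting, so there is no derivation to reproduce. For one corrected family, 1 − 0.95^1 = 0.05, as stated.

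**Step 2, networks alone.** If each network is a separate 5% family and the networks are independent, the chance of at least one false positive is 1 − 0.95^K:

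- K = 5: 1 − 0.95^5 = 0.226
- K = 10: 1 − 0.95^10 = 0.401
- K = 20: 1 − 0.95^20 = 0.642

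**Step 3, adding the seven graph and diffusion measures.** If each is tested once at 0.05 and all tests are independent, the chance is 1 − 0.95^(K+7):

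- K = 5: 1 − 0.95^12 = 0.460
- K = 10: 1 − 0.95^17 = 0.582
- K = 20: 1 − 0.95^27 = 0.750

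**Step 4, correlation.** These figures come from simulation of two-sided z tests (200,000 draws) with the same correlation between every pair:

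| Tests | Correlation 0.3 | 0.5 | 0.7 |
|---|---|---|---|
| 10 | 0.350 | 0.285 | 0.213 |
| 12 | 0.397 | 0.318 | 0.231 |
| 17 | 0.492 | 0.385 | 0.271 |

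With independent networks, and correlation of 0.5 only within the graph group and within the diffusion group, the figures are 0.430 (K = 5), 0.556 (K = 10) and 0.735 (K = 20).

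**Step 5, where one half is passed.** Thirteen independent tests give 1 − 0.95^13 = 0.487, and fourteen give 0.512. At least 14 independent tests are needed. Whether the plan reaches that depends on K and on the correlation.

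**Step 6, a stricter success rule.** Suppose Objective 5 required both a functional hit (K + 4 tests) and a structural connectivity hit (3 tests, 1 − 0.95^3 = 0.143), all independent:

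- K = 5: 0.370 × 0.143 = 0.053
- K = 10: 0.512 × 0.143 = 0.073
- K = 20: 0.708 × 0.143 = 0.101

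**Step 7, after correction across networks.** The network family returns to 0.05. A simple division puts the per-network threshold at 0.05/K: 0.01, 0.005 or 0.0025 for K = 5, 10 or 20. If the seven other measures stayed at 0.05 each as grounds for a claim, the chance would still be 1 − 0.95^8 = 0.337. Correcting the networks alone is therefore not enough; the role of the other measures must also be fixed.

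**The case against.** The strongest reply is that the text never defines the family. The words on family-wise correction do not say that it stops at one network, and a fuller protocol or analysis plan, not shown, may extend it. That is fair as to intent. However, the article does choose a threshold, ties it to voxels and places it directly after a test done network by network. Followed literally, that exceeds 5% for the objective.

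A reader might infer three stronger things that the documents do not support.

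- **That a false connectivity finding is more likely than not.** K is unstated, and under plausible K and correlation the figure falls on either side of one half (Steps 2 to 5).
- **That about a dozen further measures are tested without correction.** Brain volumes and white matter hyperintensities are not connectivity measures. For volumes, hyperintensities and graph metrics the article describes extraction, quantification or computation, not a test. The VBM and FA maps are voxel-wise, so the stated threshold can be read as covering them. The general 0.05 rule also precedes the Objective 5 text, so applying it to imaging is a reading.
- **That any single hit counts as success.** No such rule is stated. If both a functional and a structural result were required, the chance would be about 5% to 10% under independence (Step 6).

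Two further replies stand. Choosing components from the data does not by itself inflate the between-group error if the choice is blind to group. And this is a secondary objective in a self-described pilot, which limits the consequences.

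**Conclusion.** The point holds in limited form. No correction across networks is stated, within-group comparisons are admitted, and no deciding measure is named, so the 5% rate does not apply to Objective 5.

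Over networks alone the error is about 23% to 64% for 5 to 20 independent networks, and lower with correlation. It is about 46% to 75% if the seven graph and diffusion measures are each tested at 0.05, are independent, and any one positive result is taken as support. All these figures rest on the assumed K. The sound conclusion is that the error rate is uncontrolled and probably well above 5%, not that a false finding is the expected result. This deserves a change because the plan already commits to family-wise control and the extension is cheap.

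**What to change.** In Neuroimaging, fix the list of networks before any group comparison is run. State that the correction covers all of them, either by a voxel-wise family-wise threshold of 0.05/K or by one permutation maximum taken over all voxels and all networks.

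In the Data Analysis Plan, base any TPS effect under Objective 5 on the between-group difference in pre-to-post change. Label within-group comparisons, graph metrics, ADC, axial diffusivity, volumes and white matter hyperintensities exploratory. Say whether the FA and VBM maps fall under the voxel-wise threshold and what role they play. Naming one functional and one structural lead measure, with Holm across the two, is one acceptable way to settle this, but not the only one.

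The cost is wording and analysis work, plus lower sensitivity for any single network (0.005 at K = 10). No new scans should be needed, provided the waitlist arm's scan pair covers its untreated period. Trial Design ties the scans in both groups to the TPS sessions, so that timing should be confirmed in the same edit.
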